### Data Preprocessing Pipeline

Data are downloaded from Samsung Cloud onto the participant’s mobile device for transfer to the researcher’s computer for analysis. Moreover, individual nights are processed, sleep stages are integrated, and participant IDs are assigned. For quality control, nights with missing or corrupted segments are excluded, fragmented sleep data without combined scores are removed, daytime sleep (outside 7 PM to 11 AM) is excluded, nights with ≥30 minutes of stage/total discrepancies are excluded, and outliers >3 SD from baseline are flagged. For feature engineering, additional features (sleep stage percentage and real TST) are derived from the 10 device variables in ML analysis. Completeness of reporting is ensured by documenting the percentage of excluded nights and the reasons for exclusion.

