### Demographic and Geographic Context

This pilot study will be conducted in Mexico City, a metropolitan area with over 21 million residents [21]. Adults aged 30‐60 years represent over 40% of Mexico’s economically active population [22], making this demographic relevant for sleep health research. Urban workers in Mexico City face unique sleep challenges, including long commutes, shift work, and environmental stressors, that may impact sleep quality [5,23,24]. National surveys indicate that 35%‐40% of Mexican adults sleep fewer than 7 hours per night, with 37% reporting sleep problems [4,5]. Mexico City’s context provides a useful setting to explore sleep intervention feasibility in a rapidly urbanizing environment [25,26].

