### Recruitment: Participant Recruitment and Screening

The recruitment methods are as follows: (1) physical (study invitations posted on university and public hospital bulletin boards), (2) digital (study invitations on professional networking platforms like LinkedIn), and (3) referral (snowball sampling through professional networks).

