### Data Collection Quality Control

The following measures are implemented for user-related issues: (1) noncompliance: participants with missing data for >20% of nights are excluded and replaced; (2) charging issues: backup chargers are provided, and daily battery monitoring is required; (3) unauthorized modifications: settings are locked, and violations lead to replacement; and (4) sync delays: daily commitment for cloud backup within 24 hours. The following measures are implemented for device-related issues: (1) fragmented recording: nights without combined scores are excluded; (2) data mismatch: nights with artifact conflicts are excluded; and (3) sync errors: multiple attempts are made with escalating intervals. For sensor inaccuracies, quality control is performed through sleep diaries, and outliers trigger replacement. Excluded participants are replaced from the recruitment pool to maintain the sample size. The expected night exclusion impact is around 18%, with anticipated replacement ensuring the target sample.

Subjective data collection is performed through PSQI forms completed on paper. Information is manually entered by the researcher into a password-protected spreadsheet with self-verification (data are entered twice by the researcher to ensure accuracy). Data are processed through the manufacturer’s algorithms to interpret the findings of the 10 explanatory variables and the target variable (Table 1).

**Table 1. T1:** Target and explanatory variables collected by the wearable (indispensable for this study).

Variable		Description	Unit	Data type
Explanatory variable				
sleep_duration		Sum of N1, N2, N3, and REM^a^	Minutes	Integer
movement_awakening		Count of movement during sleep	Number	Integer
sleep_cycle		Count of sleep cycles	Number	Integer
mental_recovery		Score assigned according to the REM phase	Score (0‐100 scale)	Integer
physical_recovery		Score assigned according to the N3 phase	Score (0‐100 scale)	Integer
efficiency		real_total_sleep by sleep_duration	Percentage	Integer
Transition_N1		Sum of minutes of sleep in the N1 phase	Minutes	Integer
Light_N2		Sum of minutes of sleep in the N2 phase	Minutes	Integer
Deep_N3		Sum of minutes of sleep in the N3 phase	Minutes	Integer
REM		Sum of minutes of sleep in the REM phase	Minutes	Integer
Target variable				
sleep_score		Score assigned for the night	Score (1‐100 scale)	Integer

a REM: rapid eye movement.

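### The 7 PM to 11 AM window can remove the main sleep of eligible shift workers, and the two outlier rules are not reconciled

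*Protocol article*

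**What the plan says.** **Clock window.** In Data Preprocessing Pipeline, "daytime sleep (outside 7 PM to 11 AM) is excluded". No exception is given for people whose main sleep falls in the day.

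**Who may enter.** Eligibility Criteria Operationalization asks for documented full-time work of at least 40 hours a week. Neither the inclusion nor the exclusion criteria mention work schedule. Demographic and Geographic Context says: "Urban workers in Mexico City face unique sleep challenges, including long commutes, shift work, and environmental stressors". One recruitment channel is "study invitations posted on university and public hospital bulletin boards".

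**Missing nights.** Data Collection Quality Control, under noncompliance, excludes and replaces participants who lack more than 20% of nights. Adherence Assessment gives the same limit but says only that they may be excluded. The missing-data text under Statistical Methods excludes participants without enough nights in the two periods and sets no number.

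**Outliers.** Data Preprocessing Pipeline says "outliers >3 SD from baseline are flagged" and states no further action. Data Collection Quality Control says "For sensor inaccuracies, quality control is performed through sleep diaries, and outliers trigger replacement". The next sentence there reads "Excluded participants are replaced from the recruitment pool to maintain the sample size".

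**Status of these rules.** Statistical Methods states that the protocol holds the whole analysis plan and that no separate one exists, so no later document will settle these points.

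**The concern.** The primary outcome is each participant's mean sleep score over the retained nights of days 31 to 60, adjusted for the mean over days 1 to 30. The cleaning rules therefore decide what is estimated and in whom.

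A clock window suits day workers, for whom it removes naps. For an eligible person who works nights, it can remove the main sleep. Such a person may wear the watch every night, produce a score each time, and still appear to lack data. Allocation is revealed on day 0, so any resulting exclusion and replacement comes after randomisation.

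The outlier wording raises a second problem. Flagging and replacing are different actions. The text does not say whether the two sections describe one check or two, what is replaced, or whether flagged nights stay in the mean. The researcher who holds all the data learns the allocation on day 30, so this should not be left to judgement during cleaning.

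**Working it through.** **The plan's own figure.** The only number tied to night cleaning is an expected loss of around 18% of nights. It is attributed to pilot testing and literature, with no component rates, so it cannot be reproduced and the share due to the clock window cannot be separated. The gross total does reproduce: 32 × 60 = 1920 nights.

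**Clock window.** Inputs from the protocol: 60 nights per person and a limit of more than 20% missing. Assumptions: k main sleeps a week fall outside the window, and nights dropped by the window count as missing.

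- Limit: 0.20 × 60 = 12 nights, so 13 or more exceeds it.
- Share lost = k/7; nights lost = 60 × k/7.

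| Daytime main sleeps per week (k) | Share lost | Nights lost of 60 | Over the limit? |
|---|---|---|---|
| 1 | 14% | 8.6 | No |
| 2 | 29% | 17.1 | Yes |
| 3 | 43% | 25.7 | Yes |
| 5 | 71% | 42.9 | Yes |

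The answer is the same if the limit is applied to each 30-night period: 0.20 × 30 = 6 nights, against 4.3 lost at k = 1 and 8.6 at k = 2. At k = 1 the person stays in, with 12 − 8.6 = 3.4 nights left for every other cause of loss.

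If window losses do not count as missing, the person at k = 5 is kept, but the two period means rest on about 60 − 42.9 = 17 nights in total, mostly from days off.

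**Outliers, side by side.**

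| | Data Preprocessing Pipeline | Data Collection Quality Control |
|---|---|---|
| Threshold | more than 3 SD | none given |
| Reference | baseline | none given; linked to sensor inaccuracies and diaries |
| Action | flag | replacement |
| Unit acted on | not stated | not stated; the next sentence concerns participants |

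The consequence depends on the reading:

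1. Flag only, flagged nights kept: no effect on the primary mean.
2. Flagged nights deleted (stated nowhere). Assume normal nightly scores with unchanged within-person SD and a true shift of d SDs. With φ and Φ the standard normal density and distribution function, the retained shift is d + [φ(−3−d) − φ(3−d)] / [Φ(3−d) − Φ(−3−d)]. This gives 0.48 for d = 0.5 and 0.94 for d = 1.0, a modest attenuation.
3. Participants replaced because of outlying scores (also not stated as such): retention after randomisation depends on the outcome.

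**The case against.** Several points on the other side stand.

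- The protocol does not say that any shift worker was enrolled. The introduction describes the city's workers in general, and hospital notice boards sit beside university boards, a professional networking site and referrals. The number affected among 32 could be zero.
- The 20% rule is framed as noncompliance and device wear. Nothing says that a worn and scored night dropped in cleaning counts as missing. Exclusion for too few nights is still possible under the missing-data text, but without a threshold.
- The window is the same in both arms and both periods, and a habitual night worker would lose baseline nights too. Controls also receive advice on a regular schedule.
- The protocol already promises to report the percentage of excluded nights and the reasons, and it disclaims definitive inference.

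A reader might infer that the outlier rule removes people who respond to treatment. That joins the 3 SD baseline threshold of one section to the replacement action of the other. Neither section states the joined rule, and the second concerns sensor faults, so replacement may refer to a device. A rate of replaced responders computed from the joined rule would not be a magnitude for this trial.

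A reader might also infer that day workers who rise after 11 AM lose those nights. The text excludes daytime sleep and does not say what happens to an overnight session that runs past the boundary.

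What remains is that eligibility and the window disagree on daytime main sleep, and that two outlier actions stand unreconciled in the only analysis plan there is.

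**Conclusion.** The concern holds in limited form: valid main sleep can be removed, but the documents do not show that it is. If window losses count as missing, two or more daytime main sleeps a week (at least 29% of nights) put an eligible, compliant participant over the 20% limit. Each such exclusion takes one of 16 from an arm, about 6%. How many are affected is unknown. Bias between arms would need the losses to differ by arm, which is possible but not demonstrated; the firmer consequences are lost nights and an unstated narrowing of the population.

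On outliers the finding is an unresolved ambiguity, not a proven contradiction. Under flagging alone the effect is nil. It becomes serious only if replacement means participants and applies to score values. The point is worth correcting before the data are analysed and does not undermine the design as a whole.

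**What to change.** 1. Define the analysed sleep as the longest scored session in each 24 hours, whatever the clock time, and treat shorter sessions as naps. The alternative is to state a schedule restriction in the eligibility criteria, applied before randomisation. The article reports that recruitment has ended, so that alternative now serves mainly a later trial.
2. Say whether nights dropped in cleaning count towards the 20% limit.
3. Make outliers flag-only in both sections, with one definition (variable, reference, threshold). Keep flagged nights in the primary mean unless a device fault is documented, and never replace a randomised participant because of a score value.
4. Report excluded nights by arm and by period, as a breakdown of the reporting already promised.
5. Repeat the ANCOVA with all scored nights as a sensitivity analysis. The section on access control for excluded participants has their data deleted at once, so it must be reconciled with this step, within what consent allows.

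The cost is a change to the cleaning script and a few sentences. The downside is that a few noisier or atypical nights enter the means.

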### Data Management

Data entered and collected by Samsung Galaxy Watch 4 are automatically synced to Samsung Cloud (encrypted transmission) upon pairing. The PSQI forms are completed on paper, and the information is manually entered by the researcher into a password-protected spreadsheet with self-verification (data entered twice by the researcher to ensure accuracy). All data stored on the researcher’s local computer are encrypted, providing additional privacy protection through local-only storage. Moreover, data are stored in 2 separate local files as a backup measure for protection against file corruption. Access control is set, with only the researcher having access to all study data, including identifiable information linking Participant_ID to personal information. No other personnel have access to the data.

Data security involves (1) physical security (paper PSQI forms are stored in a locked filing cabinet at a secure location), (2) digital security (electronic files are password-protected and encrypted, and are stored on the researcher’s local computer only [no remote or cloud storage of identifiable data]), and (3) transmission security (Samsung device data download uses encrypted protocols [HTTPS]).

### ML-Specific Data Security Measures

ML model training is conducted on the researcher’s local computer with no internet connectivity during sensitive data processing to prevent data exfiltration. All access to ML model files and training data is logged within the researcher’s system for accountability. Cross-validation and model testing use separate data partitions, and there is no test data contamination of training sets. Validation results are stored separately from production models on the researcher’s local system. No commercial ML platforms (eg, AWS SageMaker and Google AutoML) are used to prevent corporate access to participant data. All processing uses open-source libraries (scikit-learn, XGBoost, and SHAP) on local infrastructure.

Data quality assurance includes data completeness checks (missing nights and sync failures), value range checks for physiologically implausible values, and analysis data validation using scripts for checking distributions, outliers, and duplicates.

A retention and destruction policy is implemented. Identifiable data will be retained for 5 years after publication, and then, the data will be securely destroyed (paper shredding and secure overwriting of electronic files). Deidentified data will be retained indefinitely.

### Statistical Methods

#### Primary Analysis: Single-Covariate Analysis of Covariance

The mean sleep score in the postintervention period (days 31‐60) is compared between groups using analysis of covariance with a single covariate: mean sleep score in the baseline period (days 1‐30).

$$Model:Postintervention\;score=\beta_{0}+\beta_{1}\;(group)+\beta_{2}\;(baseline\;score)+\epsilon$$

The control group is coded as “0,” and the experimental group is coded as “1.” The primary inference is based on the β₁ coefficient (group difference adjusted for baseline). The effect size is calculated as Cohen *d* with 95% CIs. Statistical significance is assessed at *α*=.05 (1-tailed per directional hypothesis), but the interpretation emphasizes the effect size magnitude and CI width, given the pilot nature of the study.

We do not use multiple covariates (age, sex beyond stratification, and behavioral factors) to avoid overfitting with the small sample size. Sex stratification in randomization addresses balance concerns without requiring covariate adjustment.

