### Sample Size: Pilot Feasibility Justification

This pilot trial enrolls 32 participants (16 per arm; stratified by sex), and this is consistent with established pilot study guidelines recommending 12‐15 participants per arm for feasibility assessment [117-120]. The sample size is explicitly designed for pilot objectives, not definitive efficacy testing.

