### Power Analysis Context: Not Designed for Definitive Testing

The sample size provides adequate power (>80%) only for very large effects (*d*≥1.0). For moderate effects typical in sleep research (*d*=0.3‐0.7), the power is insufficient, which is consistent with this study’s role as a feasibility-focused pilot trial. We explicitly acknowledge insufficient power for moderate effects. The power analysis table showing power for different effect sizes is presented in Multimedia Appendix 2. If moderate-to-large effects exist, we may detect a signal, and if effects are small, this pilot will yield null results, informing researchers that larger samples, longer interventions, or different approaches are needed. Both outcomes are valuable for the advancement of the field.

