### Accountability Framework

The accountability framework involves the following aspects:

Adverse events from artificial intelligence (AI): If ML-derived recommendations cause participant harm (eg, a recommendation to reduce sleep duration leads to excessive daytime sleepiness affecting work safety), the event is documented as an adverse event. The researcher notifies the ethics committee, and an investigation is conducted to determine if a systematic model error exists.Replication and audit: The ML code, trained models, and analysis scripts are made available to the ethics committee and peer reviewers upon request.Model performance monitoring: During the study, the principal researcher monitors whether the experimental group shows unexpected negative outcomes (eg, worsening sleep scores), triggering a review of ML recommendation patterns for systematic errors.

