Several important considerations frame the interpretation of the anticipated findings. The study acknowledges the inherent limitations of consumer wearable research, particularly reliance on Samsung’s proprietary sleep score algorithm. While this limits reproducibility of exact score computation and precludes independent PSG validation of the composite metric, the personalization framework itself is deliberately manufacturer-agnostic. Additional methodological constraints include the single-device focus, the limited geographic and cultural generalizability (Mexico City context with unique altitude, pollution, and lifestyle factors), potential measurement errors inherent to consumer-grade sensors, and the 30-day intervention period, which may be insufficient for sustained behavior change in entrenched sleep habits. The study excludes individuals with diagnosed sleep disorders, limiting the findings to healthy populations seeking sleep quality optimization rather than clinical treatment.

If validated through this pilot study, the methodology could direct sleep optimization from universal protocols toward individualized behavioral targeting, offering a scalable approach to sleep health improvement.

However, if the findings reveal no difference between personalized and generic interventions, there would be valuable evidence that (1) generic interventions may be equally effective and more cost-efficient for healthy populations, (2) the ML personalization approach requires refinement before clinical utility can be established, or (3) consumer wearables may not yet provide sufficient data quality for meaningful pattern detection at the individual level. Both positive and null findings will advance scientific understanding and inform future research directions.

The results will be available by March 2026 and will be disseminated through a peer-reviewed publication regardless of the findings (positive, null, or negative). A deidentified dataset will be part of the study output. This transparency supports scientific rigor and allows the broader research community to build upon the methodological framework regardless of this pilot’s specific outcomes.

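### The primary test is one-tailed at .05 but is reported with 95% CIs, so a significant result can have an interval containing zero; the stated power threshold is not that of the planned test, though it errs on the cautious side

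*Protocol article*

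**What the plan says.** The section on the primary analysis specifies "analysis of covariance with a single covariate: mean sleep score in the baseline period", and bases inference on the group coefficient. On the interval it says: "The effect size is calculated as Cohen *d* with 95% CIs". On the test it sets significance at α=.05, "1-tailed per directional hypothesis), but the interpretation emphasizes the effect size magnitude and CI width, given the pilot nature of the study".

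On size, "This pilot trial enrolls 32 participants (16 per arm; stratified by sex". The section on power context states: "The sample size provides adequate power (>80%) only for very large effects", with d≥1.0 as the limit, and calls power insufficient for d=0.3 to 0.7. It gives neither the sidedness nor the covariate adjustment behind these figures, and refers to a table in Multimedia Appendix 2, which is not shown. The pilot objectives list the baseline-to-follow-up correlation among the quantities to be estimated, and no value is assumed for it.

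The section on exploratory analyses says that the article holds the whole statistical analysis plan and that there is no separate one.

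**The concern.** A one-tailed test at .05 corresponds to a two-sided 90% interval. Paired with a 95% interval it leaves a band of results in which the p-value says significant and the interval includes zero. The primary result could then be reported either way, and the protocol has no rule for choosing. The conflict falls on the confidence interval, which is the quantity readers are told to rely on. The pilot is also meant to judge whether there is a signal worth a larger trial.

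The power sentence has a related fault. If its d≥1.0 threshold was computed for a different test from the planned one, readers get a detectable effect that does not belong to the primary analysis.

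**Working it through.** **Inputs from the protocol.** 16 per arm with 1:1 allocation; ANCOVA with an intercept, group and one covariate, so residual df = 32 − 3 = 29; one-tailed α=.05; 95% CIs, read as two-sided because no sidedness is given. Excluded participants are to be replaced, so 16 per arm is kept. **Assumptions.** The baseline correlation r is not given and is varied from 0 to 0.8. Variances are taken as equal.

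**1. The stated power figure.** For a two-sided unadjusted comparison by normal approximation, power at d=1.0 is Φ(1.0 × √(16/2) − 1.960) = Φ(0.868) = 80.7%, with 80% reached at d = (1.960 + 0.842)/√8 = 0.99. This reproduces the claim of above 80% only for d≥1.0. Other bases at d=1.0:

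| Basis (unadjusted, 16 per arm) | Power at d=1.0 | d for 80% |
|---|---|---|
| Two-sided, normal approximation | 80.7% | 0.99 |
| Two-sided, exact t (df 30) | 78.1% | 1.02 |
| One-sided, normal approximation | 88.2% | 0.88 |
| One-sided, exact t (df 30) | 86.8% | 0.90 |

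The match to the first row is an inference. A one-sided t test with about 13 evaluable per arm also gives about 80% (79.7%).

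**2. Test against interval.** The critical values with df 29 are t(.95) = 1.699 and t(.975) = 2.045. The standard error of the adjusted difference, in residual SD units and ignoring chance baseline imbalance, is √(2/16) = 0.3536.

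- Significant one-tailed from 1.699 × 0.3536 = 0.60 residual SD.
- 95% CI excludes zero from 2.045 × 0.3536 = 0.72 residual SD.

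The probability of falling between these, from the noncentral t with noncentrality d × √8 and d on the residual scale, is 2.5% at d=0, 11.9% at d=0.5 and 13.2% at d=0.7. Under no effect there is a further 2.5% on the unfavourable side, where the 95% CI lies wholly below zero and the one-tailed test is not significant. Total disagreement under no effect is therefore 5%.

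**3. Power of the planned ANCOVA.** The noncentrality is d × √(16/2)/√(1 − r²) with df 29, so the d for 80% power is its r=0 value times √(1 − r²). Example, one-sided at r=0.7: 0.900 × √0.51 = 0.64.

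| r (assumed) | d for 80%, one-sided .05 | d for 80%, two-sided .05 |
|---|---|---|
| 0 | 0.90 | 1.02 |
| 0.5 | 0.78 | 0.89 |
| 0.7 | 0.64 | 0.73 |
| 0.8 | 0.54 | 0.61 |

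At r=0 the one-sided ANCOVA has 86.8% power at d=1.0, and any positive r raises it.

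**4. The range called underpowered, d=0.3 to 0.7.** For d=0.7 with a two-sided test, 80% power needs √(1 − r²) = 0.7/1.025 = 0.683, so r of about 0.73. At r=0.5 the power is 60% and at r=0.7 it is 76%. For d=0.5 it is only 62% at r=0.8. With the one-sided test, d=0.7 has 61% power at r=0, 72% at r=0.5 and 86% at r=0.7.

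**The case against.** The one-tailed choice is disclosed, and the protocol plays down significance: it directs interpretation to effect sizes and intervals, calls all findings preliminary and disclaims definitive testing. No confirmatory claim turns on .05 against .025. This stands, and it limits the consequence. It does not say what to report when test and interval differ.

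A reader might infer that the power figure is simply wrong, or that baseline adjustment was ignored. The documents do not support either. The appendix table is not shown, the figure reproduces under one common approximation, and power above 80% at d≥1.0 is true for the planned test. Only the word "only" is off, and it is off in the cautious direction. Leaving r unassumed is defensible, since the pilot is to estimate it. The protocol also warns that variance may be larger in the experimental arm, which would reduce power below the equal-variance figures here.

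A reader might also argue that a one-tailed test contradicts the protocol's own expectation of possible harm. The supporting text is a promise to disseminate "regardless of the findings (positive, null, or negative" and in-study monitoring of whether the experimental group "shows unexpected negative outcomes (eg, worsening sleep scores". The first concerns publication and the second a review of recommendations; neither is an inferential claim. The 95% CI would itself show a harmful effect.

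**Conclusion.** The mismatch between test and interval is real and sits in the primary inference. It affects adjusted effects of about 0.60 to 0.72 residual SD, with a favourable-side probability of 2.5% under no effect and about 12% to 13% at residual-scale d of 0.5 to 0.7. This rests on 29 residual df and on reading the 95% CI as two-sided.

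The power sentence does not describe the planned one-tailed ANCOVA, which reaches 80% at d=0.90 or lower. That error is conservative, its origin is inferred, and its size depends on a correlation that the protocol does not give. The statement that power is insufficient for d=0.3 to 0.7 holds for most of that range and needs a qualifier at the upper end, not withdrawal. The point should be corrected, but in a pilot that emphasises estimation it does not undermine the trial.

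**What to change.** 1. Align test and interval before outcomes are analysed. Either make the test two-sided at .05 and keep the 95% CI, or keep the one-sided .05 test and report a 90% CI. Both remove the conflict. The two-sided route raises the detectable effect by about 14% (1.025/0.900 = 1.14); the one-sided route leaves it unchanged.

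2. Restate the power sentence for the chosen ANCOVA, naming its sidedness and marking the correlation as an assumption. For r = 0, 0.5, 0.7 and 0.8, 80% power is reached at d of about 1.02, 0.89, 0.73 and 0.61 two-sided, or 0.90, 0.78, 0.64 and 0.54 one-sided. State the basis of the appendix table in the same terms.

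3. Qualify the statement on d=0.3 to 0.7: the upper end may reach 80% power if r is high (about 0.73 or more for d=0.7, two-sided).

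All three are changes of text. None alters the sample size, data collection or the model.

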### Trial Design

This is a parallel-group randomized controlled pilot trial with a 1:1 allocation ratio. Participants are stratified by sex (male/female) and randomized to either (1) a control group receiving generic sleep hygiene education or (2) an experimental group receiving personalized ML-derived behavioral recommendations.

The observation period is 60 days, which aligns with PSQI requirements for 30-day data collection periods. PSQI assessments are performed at (1) baseline (prior to device use), (2) day 30 (first monitoring period), and (3) day 60 (postintervention period). This enables subjective-objective correlation while establishing a baseline (days 1‐30) to be used as a covariate for intervention analysis (days 31‐60). While 30 days may be minimal for entrenching behavior change, this pilot will establish feasibility and preliminary effect sizes for future extended trials.

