### Assignment of Interventions (Allocation)

Sequence generation is performed through computer-generated randomization using Python (numpy.random.RandomState with seed=42 for reproducibility). Participants are stratified by sex (male/female) to ensure balance. Block randomization with randomly permuted block sizes (2, 4, 6) is used to maintain unpredictability while ensuring approximately equal group sizes throughout recruitment. The approach is implemented using numpy, hashlib, and pandas libraries.

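### Sex is a stratification factor but is left out of the primary ANCOVA; if sex predicts the score beyond baseline, the planned interval is too wide and the test conservative

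*Protocol article*

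**What the plan says.** Under Trial Design, "Participants are stratified by sex (male/female) and randomized" to one of two arms. Assignment of Interventions gives the purpose, "Participants are stratified by sex (male/female) to ensure balance", and the method: "Block randomization with randomly permuted block sizes (2, 4, 6) is used to maintain unpredictability". The planned size is 32, 16 per arm.

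Under Primary Analysis, the mean postintervention score is "compared between groups using analysis of covariance with a single covariate: mean sleep score in the baseline period" (days 1 to 30). The model equation has an intercept, a group term and a baseline term. Sex is left out deliberately, for two reasons. The first is overfitting: "We do not use multiple covariates (age, sex beyond stratification, and behavioral factors) to avoid overfitting with the small sample size". The second is the design: "Sex stratification in randomization addresses balance concerns without requiring covariate adjustment".

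The same section sets a one-tailed 5% level but puts the weight of interpretation on effect size and interval width. The Exploratory Analyses section says that the article holds the whole analysis plan and that there is no separate one, so the sex term is not deferred to another document.

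**The concern.** The sentence on stratification joins two claims, and only one is right. Balance on sex means that sex cannot bias the comparison. Balance also removes the sex contribution from the true sampling variance of the group difference. A model without sex does not know this. It leaves the between-sex variance in the residual and computes its standard error as if sex had been free to fall unevenly between arms. Stratifying is therefore a reason to include the factor.

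The overfitting reason is weak for this factor. One binary term is not the same as adding age, sex and several behavioural factors together.

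What is at stake is the reported precision. Interval width is what the plan says it will interpret, and Pilot Objectives makes within-group variability an input to the next trial. The protocol also concedes that power is insufficient for moderate effects.

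**Working it through.** **Inputs from the protocol article.** N = 32, 16 per arm; stratification by sex; permuted blocks of 2, 4 and 6; planned model of group plus baseline; one-sided 5% level; stated power above 80% at d of 1.0 or more.

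**Inputs assumed, because the article gives none.** Baseline-to-follow-up correlation 0.6 (0.7 in a second run); 16 men and 16 women unless noted; sex difference given baseline, γ, from 0 to 1.0 residual SD.

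**1. The plan's own figure.** For two groups of 16 the noncentrality at d = 1.0 is 1.0 × √(16/2) = 2.828. The exact t with 30 df gives 86.8% one-sided. Two-sided it is 78.1%, or 80.7% by the normal approximation. The stated power holds for the one-sided test that the plan uses. It involves no sex effect, so it does not settle this point.

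**2. Cost of the term.** Residual df fall from 32 − 3 = 29 to 32 − 4 = 28. The critical value rises by 0.16% two-sided and 0.12% one-sided.

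**3. Size by formula.** If a proportion p of participants are men and the arms are balanced within sex, omitting sex multiplies the residual variance by about 1 + p(1 − p)γ². With p = 0.5, the reported SE is inflated by √(1 + 0.25γ²):

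- γ = 0.2: √1.010 = 1.005
- γ = 0.5: √1.0625 = 1.031
- γ = 0.8: √1.16 = 1.077
- γ = 1.0: √1.25 = 1.118

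**4. Simulation of the design.** Correlation 0.6; 20,000 trials per row for width, error and coverage; 8,000 for one-sided power at a true difference of 0.7 SD of the score within sex.

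| γ | CI width, with sex ÷ without | One-sided type I, without / with sex | 95% CI coverage, without sex | Power, without / with sex |
|---|---|---|---|---|
| 0 | 1.002 | 5.0% / 5.1% | 95.1% | 76.5% / 76.1% |
| 0.2 | 0.997 | 4.8% / 5.0% | 95.2% | 76.4% / 76.7% |
| 0.5 | 0.971 | 4.6% / 5.1% | 95.9% | 75.0% / 77.0% |
| 0.8 | 0.927 | 3.9% / 5.0% | 96.5% | 72.9% / 77.0% |
| 1.0 | 0.891 | 3.4% / 5.0% | 97.0% | 70.3% / 77.1% |

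The Monte Carlo error on type I error is about √(0.05 × 0.95 / 20,000) = 0.15 points. Compared with the true spread of the estimate, the planned model's SE is too large by about 2%, 6% and 10% at γ = 0.5, 0.8 and 1.0.

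**5. Second run.** Correlation 0.7, d = 0.6, 6,000 trials per setting. Type I error without sex was 5.2%, 4.5% and 3.3% at γ = 0, 0.5 and 1.0. Power without / with sex was 73.2% / 72.9%, 72.2% / 73.8% and 65.4% / 72.4%. At γ = 1.0 the mean reported SE was 0.288 against a true 0.256, a ratio of 1.125.

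**6. Where the loss shrinks or vanishes.**

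- Uneven split, γ = 0.5. At 10/22, p(1 − p) = 0.215 and the formula gives a width ratio of 1/√1.0537 = 0.974 (simulated 0.976). At 6/26, p(1 − p) = 0.152 and it gives 1/√1.0381 = 0.981 (simulated 0.983).
- Sex acting only through the baseline score. The simulated width ratio is 1.005 and coverage without sex is 95.2%, so nothing is lost.

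**The case against.** The strongest reply is that the covariate already in the model does most of the work. Each participant's own 30-night mean comes from the same device and score, so a stable difference between men and women would be largely absorbed by it. Only a sex difference in what happens after day 30, given baseline, is left to inflate the residual. The article gives no value for that, and a full residual SD would be large. This stands. A reader might infer that the planned interval will be too wide and the test conservative. The documents support only the conditional statement.

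A reader might also infer that the estimate is biased, or that the benefit of stratifying is thrown away. Neither follows. The estimate is unbiased, coverage never falls below nominal, and the lower true variance is kept. Only the reported SE fails to show it.

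It can also be said that this is a pilot whose results are to be read as preliminary, so a few points of power change no decision. That limits the severity. It does not rescue the stated rationale, because interval width is what the plan proposes to interpret and the remedy is nearly free.

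**Conclusion.** The mismatch between design and model is explicit, and the reason given for it is half right: sound on bias, wrong on the standard error. The consequence is conditional and on the safe side. With a 16/16 split and a baseline correlation of 0.6 to 0.7, both assumed, there is no meaningful loss up to a residual sex difference of 0.2 SD. At 0.5 SD the loss is about 3% of interval width and about 2 points of power, with the test at about 4.5%. At 1.0 SD it is about 11% of width and about 7 points of power, with the test at about 3.4%. The documents do not say where in this range the trial lies. Minor severity. The case for change rests on asymmetry: the term costs almost nothing if sex is irrelevant and restores the correct width and error rate if it is not.

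**What to change.** Make the primary model: postintervention score = b0 + b1(group) + b2(baseline score) + b3(sex) + error, with inference on b1 as now. Replace the sentence on stratification with one saying that sex is included because randomisation was stratified by it. Keep the decision not to add age and behavioural factors.

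The cost is 1 of 29 residual degrees of freedom. If sex is irrelevant, that is under half a point of power (0.4 points in one run, 0.3 in the other). The term also absorbs any sex imbalance left by incomplete blocks or exclusions.

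Date and record the change before outcomes are analysed. If they have already been seen, keep the planned model as primary and report the sex-adjusted one beside it as a labelled sensitivity analysis.

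The change concerns the primary model only. PSQI change is compared by an independent-samples t test, which has no covariate model to extend.
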